### 2.6. Outcomes (Table 1)

#### 2.6.1. Primary Feasibility Outcomes

The primary feasibility outcomes are as follows:Recruitment ≥ 5/month (30 cases/6 months);Retention rates ≥ 70%;Patient tolerance and acceptability of the HFNC during dental treatment ≥ 80%;Completeness of physiological and questionnaire-based data collection ≥ 80%;Occurrence of device-related adverse events at less than 5% (less than one case).

**Table 1 dentistry-14-00208-t001:** Outcomes table.

Category	Outcome	Purpose
Primary (Feasibility)	Recruitment, retention	Trial feasibility
	Acceptability, tolerance	Practical implementation
	Data completeness	Outcome feasibility
	Adverse events	Safety
Secondary (Exploratory)	Pulse rate, respiratory rate	Stress physiology
	HRV (LF/HF)	Autonomic response
	EEG alpha activity	Neurophysiological stress
	Questionnaire	Patient-centered outcomes

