#### 2.6.3. Statistical Analysis

As this is a pilot feasibility study, formal hypothesis testing is not planned. Feasibility and exploratory outcomes will be summarized descriptively. Analyses of secondary outcomes will be exploratory and intended to inform the design of future definitive trials. Regarding continuous outcomes, we will estimate the mean difference between treatment with a HFNC and treatment without a HFNC, along with its 95% confidence interval.

In the case of missing data, the proportion of missing values will be reported for each variable at each time point. Summary statistics will be calculated excluding missing values. Differences between time points will be assessed after excluding subjects with missing values, as this study will include only two time points.

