Additionally, the HFNC may improve the coordination between breathing and swallowing [3,4,5,6,7,12], a function that is critically challenged during dental procedures. A recent scoping review highlighted the conflicting results of studies that have explored the effects of the HFNC on swallowing function and swallowing–breathing coordination, confirming the need for context-specific feasibility studies before definitive effectiveness trials are undertaken [6]. These considerations further support the rationale for evaluating the HFNC under dental-specific conditions, rather than extrapolating findings from perioperative or critical care settings [1]. The primary objective of this pilot study is not to establish the clinical effectiveness of the HFNC in reducing stress but to determine whether its use during dental treatment might be feasible, acceptable to patients, and compatible with routine dental workflows. The assessed feasibility outcomes, including patient tolerance, acceptability, data completeness, and device-related safety, are essential prerequisites for the successful design and execution of future definitive clinical trials. Importantly, this study intends to demonstrate that HFNCs can be used in dental clinics and that comprehensive physiological and patient-reported data can be collected without disrupting standard dental procedures.

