## 4. Conclusions

This RCT study is designed to assess the feasibility, acceptability, safety, and preliminary physiological effects of HFNC during periodontal treatment. By focusing on feasibility-related outcomes and exploratory patient-centered measures, this pilot study provides a methodological and physiological rationale for conducting a fully powered clinical trial to evaluate the effectiveness of the HFNC for improving breathing comfort and reducing treatment-related stress in routine dentistry in future-oriented studies.

These findings may suggest that delivering warmed and humidified high-flow air may address common sources of discomfort during dental treatment, particularly difficulties related to nasal breathing and swallowing saliva, which may contribute to dental anxiety. Although no conclusions regarding clinical effectiveness can be drawn from this exploratory pilot study, the results support subsequent confirmatory trials.

Ultimately, further research informed by these feasibility data has the potential to establish the HFNC as a novel, low-burden, patient-centered adjunct to routine dental care, with implications for improving treatment tolerance, safety, and overall oral health outcomes.

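### Five primary feasibility thresholds are set, but nothing ties the go-ahead to meeting them, and the Conclusions already declare support for a confirmatory trial

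*Protocol article*

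**What the plan says.** - Protocol article, 2.6.1 Primary Feasibility Outcomes, gives five criteria, each with one cut-off. The list begins "The primary feasibility outcomes are as follows:Recruitment ≥ 5/month (30 cases/6 months);Retention rates ≥ 70"% and continues with "Patient tolerance and acceptability of the HFNC during dental treatment ≥ 80"%; "Completeness of physiological and questionnaire-based data collection ≥ 80"%; and device-related adverse events below 5%, glossed in brackets as fewer than one case. Table 1 assigns purposes to these outcomes but no ranking and no rule for combining them.
- 2.6.3 Statistical Analysis: "Feasibility and exploratory outcomes will be summarized descriptively".
- 2.6.4 Sample Size puts the supply of eligible patients at about 30 per year and the target at 30 participants.
- 3 Discussion says that the assessed feasibility outcomes, with tolerance, acceptability, completeness and device safety given as examples, "are essential prerequisites for the successful design and execution of future definitive clinical trials".
- 4 Conclusions: "Although no conclusions regarding clinical effectiveness can be drawn from this exploratory pilot study, the results support subsequent confirmatory trials".

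**The concern.** The primary objective is to assess whether a definitive trial is feasible. A numeric cut-off serves that objective only if something follows from meeting or missing it, and here nothing does. The Discussion implies that the criteria are necessary conditions; the Conclusions give the go-ahead without condition. The opening clause of that sentence disclaims clinical effectiveness only, so it does not soften the statement about proceeding.

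Taken as written, a study that misses a threshold, tolerance for example, still ends with the favourable conclusion. If some criteria are met and others missed, whoever writes the report chooses how to weigh them once the results are known.

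**Working it through.** **1. The plan's own figure.** 5 per month × 6 months = 30, as 2.6.1 states.

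**2. Is a mixed result likely?** From 2.6.4, 30 per year ÷ 12 = 2.5 eligible per month, and 2.5 × 6 = 15 in six months even if everyone consents. Assuming Poisson arrivals with mean 15, P(at least 30) = 1 − Σ(k = 0 to 29) e^(−15) 15^k / k! = 0.0004. On the stated flow, recruitment is very likely to be missed while other criteria may be met.

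The adverse-event line adds a second ambiguity: 5% of 30 is 1.5 cases, and 1/30 = 3.3% is below 5% but is not fewer than one case. Both readings (0 cases; at most 1 case) are carried below.

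**3. How much does the unstated rule matter?** The article gives no expected rates, so these are assumptions, as is independence between criteria. Recruitment is left aside and 30 enrolled are taken as the denominator throughout. Cut-offs: retention 70% = 21 of 30; tolerance and completeness 80% = 24 of 30.

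Scenario with poor tolerance (true retention 70%, tolerance 60%, completeness 90%, device adverse events 2%), binomial tails:
- P(retention ≥ 21) = 0.589
- P(tolerance ≥ 24) = 0.017
- P(completeness ≥ 24) = 0.974
- P(0 events) = 0.98^30 = 0.545; P(at most 1) = 0.879

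All four met: 0.589 × 0.017 × 0.974 × 0.545 = 0.005, or 0.009 with at most one event.

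At least three of four: 0.32, or 0.51 with at most one event. Most of this comes from studies that miss tolerance alone: 0.589 × 0.983 × 0.974 × 0.545 = 0.31, or 0.50 with at most one event.

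The unit and denominator of the criteria are not stated. If tolerance and completeness are judged among those retained, with events counted over either the enrolled or the retained, all four are met in 0.8–1.3% of studies and three of four in 32–53%. Across all these readings the contrast is about 1% against roughly 32–53%.

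**4. A more favourable scenario** (retention 85%, tolerance 90%, completeness 90%, adverse events 2%, all on 30 enrolled):
- Recruitment met: P(all five) = 0.51 with zero events required, 0.83 with at most one.
- Recruitment at the stated flow, with 30 eventually enrolled: P(all five) = 0.0002–0.0003; P(at least four) = 0.51–0.83.

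Even when HFNC is well tolerated, the verdict turns on whether one missed criterion is disqualifying.

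**The case against.** The best case on the other side has four parts.

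- **A condensed article may leave a progression rule to the full protocol or analysis plan.** This is fair, and absence alone would not be a finding. But the article itself prints the thresholds, calls the outcomes prerequisites and then states an unconditional go-ahead. That conflict is in the text shown, and a rule held elsewhere would not remove it.
- **Reporting each criterion descriptively against its own threshold is a legitimate pilot design.** This also stands, and no hypothesis test is being asked for. A reader might go further and infer that the study cannot return a negative answer. The article does not support that: each threshold can visibly fail. What is missing is the consequence of failing.
- **The Discussion does not rank the criteria.** A reader might infer from its list that tolerance, completeness and safety are decisive and that recruitment and retention are secondary. The list is introduced as examples, and 2.6.1 counts recruitment and retention among the primary outcomes, so no such hierarchy can be drawn from it. The sentence leans towards all criteria being required.
- **The size depends on assumptions.** This is true. The true rates are assumed, and independence is doubtful because intolerance or an adverse event could also reduce completeness. With favourable rates and recruitment met, all five are met in 51–83% of studies, so a mixed result is not inevitable at 30 patients. It is likely because of the stated patient flow.

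**Conclusion.** The point holds as a conflict within the article on its primary question: thresholds that can be missed, described as prerequisites, beside a favourable conclusion that does not depend on them. That a mixed result is likely rests on the article's own figures (about 15 eligible in six months against 30 required), given the stated flow and, for the probability of 0.0004, Poisson arrivals. The effect of the unstated rule, about 1% against roughly 32–53%, is an illustration under assumed rates with 60% tolerance and independent criteria.

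A reader might stretch the range to about 99% by counting any single met threshold as success. Nothing in the article suggests that rule, so the wider range should not be used.

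The gap should be closed before enrolment. It affects how the primary objective is answered, not the data collected.

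**What to change.** 1. **Reconcile two criteria first**, so that a rule can be applied: recruitment (30 in six months in 2.6.1 against about 30 eligible per year in 2.6.4) and device-related adverse events (below 5% against fewer than one case).
2. **Add a rule to 2.6.1 before enrolment.** In line with the Discussion, a definitive trial as designed is supported only if all five thresholds are met. Any missed threshold is reported as missed, and the conclusion is then limited to a trial modified on that named point or to not proceeding. The sponsor may name which criteria are amendable, but must do so before enrolment.
3. **Reword section 4** so that support for a confirmatory trial is conditional on that rule.

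The cost is wording only: no added patients, data or tests, and the descriptive analysis in 2.6.3 can stay. The sponsor gives up the discretion to call a mixed result favourable. Unless recruitment is reconciled first, meeting all five would be almost out of reach on the stated patient flow.

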## 2. Methods

### 2.1. Study Design

This is an investigator-initiated, single-center, open-label pilot feasibility study that will be conducted at Nagasaki University Hospital, Japan. The study was designed in accordance with the Consolidated Standards of CONSORT extension for pilot and feasibility trials and the principles of the Declaration of Helsinki. Ethical approval was obtained from the Clinical Research Review Board of Nagasaki University, and the study is registered with the Japan Registry of Clinical Trials (jRCTs072240099). Given the exploratory nature of the research question and the need to evaluate feasibility-related parameters before a definitive trial, a pre–post, fixed-sequence, within-subject feasibility design was adopted.

As illustrated in Figure 1, this pilot study was specifically designed as a feasibility-oriented, pre–post, fixed-sequence, within-subject study to evaluate the practicality, acceptability, and safety of high-flow nasal cannula (HFNC) use during routine full-mouth periodontal treatment, rather than to assess clinical effectiveness. Participants will undergo two dental treatment sessions, one without a HFNC and one with a HFNC, separated by a washout period of at least four weeks.

The research design, measurement items, and evaluation indicators for high-flow nasal cannula (HFNC) intervention in full-mouth periodontal treatment are shown in Figure 1, which illustrates the structured approach to evaluating the impact of a HFNC during full-mouth periodontal treatment in a fixed-sequence, pre–post, within-subject feasibility design.

Research design (Pre–Post, Fixed-Sequence, Within-Subject Feasibility Design): The study will be conducted in two sessions separated by a washout period of 4 weeks.

Session 1 (Baseline Data Collection): Dental treatment will be performed under standard conditions without a HFNC to establish baseline physiological and psychological data.

Session 2 (HFNC Intervention): Dental treatment will be performed while delivering 20–30 L/min of heated and humidified air via a HFNC to measure the intervention’s impact.

Measurement items: Data collected include physiological indicators such as Pulse Rate (PR), Heart Rate Variability (HRV: LF/HF), Respiratory Rate (RR), and Brain Waves (EEG alpha), as well as patient-centered metrics like Quality of Life (QOL) and Satisfaction.

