### 2.2. Participants

Adult patients (aged ≥ 18 years) undergoing routine full-mouth periodontal treatment at the Department of Special Care Dentistry, Nagasaki University Hospital, will be eligible for inclusion. Written informed consent will be obtained from all participants prior to enrolment.

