### 2.3. Inclusion Criteria

Patients visiting the Nagasaki University Hospital Dental Department for regular management and scheduled to undergo full-mouth periodontal disease treatment (periodontal pocket cleaning);Age ≥ 18 years at the time of consent;Ability to understand the study procedures and complete questionnaires independently.

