#### 2.6.4. Sample Size

As this is a pilot feasibility study, a formal sample size calculation based on statistical power was not performed. Approximately 30 patients per year who meet the eligibility criteria are treated at the Department of Special Care Dentistry of Nagasaki University Hospital. Therefore, a target sample size of 30 participants was considered feasible within the planned study period and sufficient to assess feasibility outcomes, including recruitment, acceptability, data completeness, and safety, to inform the design of future definitive trials.

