### Limitations

This study has several limitations. First, it is a single-center, open-label, pilot feasibility study, and the findings are not intended to be generalizable or establish clinical efficacy. The exploratory analyses are not powered for hypothesis testing. Therefore, the results should be interpreted cautiously. However, these characteristics are inherent in pilot feasibility studies and are appropriate, given the primary objective of informing future study designs.

Second, the target sample size was determined pragmatically based on the annual number of eligible patients at the study institution and the anticipated consent rates, rather than on formal power calculations. Nevertheless, the comprehensive collection of physiological (EEG and ECG) and patient-reported data provides valuable preliminary information to guide the outcome selection and sample size estimation for subsequent confirmatory studies.

Third, the open-label, pre–post, fixed-sequence, within-subject feasibility design may be susceptible to expectation and sequence effects despite the inclusion of a washout period. In addition, stress and comfort will partly be assessed using self-reported questionnaires, which may be influenced by prior experience or recall bias.

Fourth, this study will use a fixed-sequence, within-subject comparison with the first full-mouth periodontal treatment without a HFNC, followed by a second session with a HFNC to minimize patient anxiety regarding HFNC use. Informed consent will be obtained before the interventions. However, a randomized crossover study design would be more appropriate for the objective evaluation of outcomes, as such a design could minimize the influence of period effects, learning or conditioning effects, and expectation bias, particularly when subjective endpoints such as comfort and anxiety are assessed. In the future, randomized crossover designs should be further examined.

Finally, the study will involve only patients undergoing full-mouth periodontal treatment (each session will be 30 min or less, with the patient in the supine position and no rubber dam). Future studies investigating the use of a HFNC during other dental procedures, such as extractions or endodontic therapy, are warranted. Furthermore, caution will be required when extrapolating these findings to other dental treatment contexts.

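### The recruitment criterion (30 in 6 months) does not fit the stated 30 eligible patients per year: it needs twice the eligible flow, or every patient in a standing pool

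*Protocol article*

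**What the plan says.** Section 2.6.1 (Primary Feasibility Outcomes) opens its list of thresholds with "Recruitment ≥ 5/month (30 cases/6 months".

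Section 2.6.4 (Sample Size) gives the supply of patients: "Approximately 30 patients per year who meet the eligibility criteria are treated at the Department of Special Care Dentistry of Nagasaki University Hospital". It concludes that "a target sample size of 30 participants was considered feasible within the planned study period", but does not say how long that period is.

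The Limitations describe the target as "based on the annual number of eligible patients at the study institution and the anticipated consent rates". No consent rate appears anywhere in the article.

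Two further statements fix where patients come from. Section 2.1 says "This is an investigator-initiated, single-center, open-label pilot feasibility study", so no second site adds patients. Section 2.2 draws on the same department that section 2.6.4 counts: adults "undergoing routine full-mouth periodontal treatment at the Department of Special Care Dentistry, Nagasaki University Hospital, will be eligible for inclusion". Section 2.3 adds that they are "Patients visiting the Nagasaki University Hospital Dental Department for regular management", which bears on whether the 30 are new arrivals or returning patients.

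**The concern.** The same number, 30, is the enrolment required in six months and the number of eligible patients treated in a year. Nothing in the article reconciles the two.

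Recruitment is a primary outcome of a study whose purpose is to find out whether a definitive trial is feasible. If the threshold is above what the stated supply can deliver, or leaves no room for a single refusal, missing it tells the reader little about patients' willingness to take part. The pass/fail label would then be set by the choice of threshold.

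**Working it through.** **Inputs**

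- Criterion: at least 5 per month, 30 in 6 months (section 2.6.1).
- Eligible patients: about 30 per year (section 2.6.4).
- Target: 30 participants (section 2.6.4).
- Sites: one (section 2.1); source department the same as the one counted (sections 2.2 and 2.6.4).
- Consent rate: not given. I assume a range of 50% to 100%.

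**The plan's own figure**

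5 per month × 6 months = 30, so the criterion is consistent within itself.

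**Reading A: the 30 are a flow, arriving through the year**

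- Monthly flow: 30 / 12 = 2.5.
- Six-month flow: 2.5 × 6 = 15. This does not reproduce 30.
- Ratio of criterion to flow: 5 / 2.5 = 2.
- Twelve-month flow: 2.5 × 12 = 30. This does reproduce the target, at full consent.

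With consent rate c, the enrolment rate is 2.5 × c per month and the time to 30 is 30 / (2.5 × c):

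| Assumed consent | Per month | In 6 months | Months to 30 |
|---|---|---|---|
| 100% | 2.5 | 15 | 12 |
| 80% | 2.0 | 12 | 15 |
| 70% | 1.75 | 10.5 | 17.1 |
| 50% | 1.25 | 7.5 | 24 |

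The annual figure is approximate, so I checked how far it would have to be out. Taking eligible arrivals as Poisson with mean (annual number / 2) and consent as 100%, the probability of 30 or more in six months is:

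| Eligible per year | Mean in 6 months | P(30 or more) |
|---|---|---|
| 30 | 15 | 0.0004 |
| 36 | 18 | 0.006 |
| 40 | 20 | 0.022 |
| 60 | 30 | 0.52 |

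An even chance needs about 60 eligible patients per year at full consent. At assumed consent c, 5 per month needs 60 / c per year: 75 at 80% and 120 at 50%.

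**Reading B: the 30 are a standing pool of returning patients**

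Suppose all 30 attend, and can be approached, within six months.

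- Consent needed: 30 / 30 = 100%.
- Enrolled at assumed consent of 80%, 70% and 50%: 30 × 0.8 = 24, 30 × 0.7 = 21, 30 × 0.5 = 15.
- Per month: 24 / 6 = 4, 21 / 6 = 3.5, 15 / 6 = 2.5. All are below 5.

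The conflict is smaller here, but it remains as soon as anyone declines.

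**The case against.** The strongest reply is that section 2.6.4 says only how many eligible patients are treated in a year, not that they arrive evenly. Recruiting people who attend for regular management may well mean recruiting from a list of returning patients. In that case most or all could be approached in six months, and the criterion would be met if everyone agreed. This stands. A reader might infer that the criterion must fail even at full consent, but that holds only on the flow reading, and the article does not settle which reading applies. The factor of two, the Poisson figures and the months to reach 30 all belong to that reading.

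Second, a reader might infer that calling 30 feasible within the planned period has no basis. That goes too far. The period's length is not given, the six months appear only in the criterion, and twelve months at full consent yields exactly 30. What can be said is that the period is unstated and that this arithmetic allows for no refusals.

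Third, section 2.3 names the hospital's Dental Department, which might suggest a larger source. Sections 2.2 and 2.6.4 both name Special Care Dentistry, and section 2.3 can be read as the broader setting containing it. I do not rely on this as a separate inconsistency. If the wider department really is the source, the eligible count in section 2.6.4 is the figure to correct.

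Fourth, section 2.6.3 plans descriptive summaries, and no stop/go rule is tied to the threshold. The observed rate will be reported and will help plan a later trial. That is right, and it limits the harm to the pass/fail judgement. It does not remove the mismatch, because a numeric threshold has been set and the result will be read against it.

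**Conclusion.** Sections 2.6.1 and 2.6.4 conflict as written. If about 30 per year is a flow, the criterion asks for twice the eligible patients (5 against 2.5 per month; 30 against 15 in six months) and is almost certain to be missed, with a probability of about 0.0004 of enough eligible patients even at full consent. If it is a standing pool, the criterion needs 100% enrolment, which sits badly with the claim that consent rates were considered.

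On both readings, failing the criterion would mainly reflect a mis-set threshold. It would not follow that the study learns nothing about recruitment, since the observed rate remains useful.

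The conclusion rests on the stated count being roughly right and on the single named department being the source. The Poisson figure also assumes independent arrivals at a constant rate. The consent rates used are assumptions, because the article gives none.

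**What to change.** Reconcile sections 2.6.1 and 2.6.4 in one of two ways, depending on which figure is wrong.

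1. If the eligible count is right, set the monthly threshold and the recruitment window from that count times the anticipated consent rate. On the flow reading this means at most 2.5 per month and at least 12 months for 30 participants. For illustration, assumed consent of 80%, 70% and 50% gives about 15, 17 and 24 months. On the pool reading, say that the 30 are returning patients and set a number below 30 that allows for refusals.
2. If 30 in six months is right, correct the eligible count in section 2.6.4 and say which department or departments it covers.

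In either case, state the anticipated consent rate and the planned recruitment period, and report the number consented over the number of eligible patients approached alongside the monthly rate. That proportion measures willingness directly and needs only a screening log.

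The first option costs a lower stated threshold or a longer stated window. Because the study is registered and has ethical approval, changing a primary feasibility criterion also needs a protocol amendment.
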